## Abstract

**Background:**

Occupational health professionals may play an important role in preventive health promotion activities for employees. However, due to a lack of knowledge and evidence- and practice based methods and strategies, interventions are hardly being implemented by occupational physicians to date. The aim of the Balance@Work project is to develop, evaluate, and implement an occupational health guideline aimed at the prevention of weight gain among employees.

**Methods:**

Following the guideline development protocol of the Netherlands Society of Occupational Medicine and the Intervention Mapping protocol, the guideline was developed based on literature, interviews with relevant stakeholders, and consensus among an expert group. The guideline consists of an individual and an environmental component. The individual component includes recommendations for occupational physicians on how to promote physical activity and healthy dietary behavior based on principles of motivational interviewing. The environmental component contains an obesogenic environment assessment tool. The guideline is evaluated in a randomised controlled trial among 20 occupational physicians. Occupational physicians in the intervention group apply the guideline to eligible workers during 6 months. Occupational physicians in the control group provide care as usual. Measurements take place at baseline and 6, 12, and 18 months thereafter. Primary outcome measures include waist circumference, daily physical activity and dietary behavior. Secondary outcome measures include sedentary behavior, determinants of behavior change, body weight and body mass index, cardiovascular disease risk profile, and quality of life. Additionally, productivity, absenteeism, and cost-effectiveness are assessed.

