#### Step 2. Performance and change objectives

The second step of IM further specified the expected changes as a result of the intervention in four program objectives. Next, performance objectives were specified for each of the four program objectives (what workers are supposed to do as a result of the program), from which the most important and changeable behavioral and environmental determinants were selected [20].

The first task was to translate the selected personal risk behaviors of the needs assessment into health-promoting behavior, based on existing literature and results from the interviews. Two program objectives for increasing physical activity and two program objectives for increasing healthy dietary behavior were identified (table 1). With respect to physical activity behavior, increasing physical activity across all domains (i.e. transport-related, work-related, leisure time and sports) was encouraged. Moreover, due to the fact that sitting time during work increased over the last decades and that sedentary behavior is regarded as an independent risk factor of adverse health [33], decreasing sedentary behavior was specified as an objective. Regarding nutrition, the consumption of fruit was promoted, and a decrease in consumption of snacks was stimulated. The consumption of soft drinks was not targeted as only small observational studies found an association between soft drinks and weight gain in adults [34,35].

**Table 1 T1:** Program objectives of the Balance@Work project.

1. Employees increase their levels of physical activity
2. Employees decrease their levels of sedentary behavior
3. Employees increase their consumption of fruit
4. Employees reduce their energy intake derived from snacks

The next step was to specify performance objectives for each of the program objectives. These constitute the specific behavioral outcomes of the program expected from the target group. Specification of the performance objectives was done via a combination of methods, namely a review of the literature, interviews with relevant stakeholders and a review of theoretical models such as Goal setting theory [36], Implementation intentions [37], the Theory of Planned Behavior [38], the Precaution Adoption Process Model [39], and the EnRG framework [40]. Based on the self-regulation theory, eight performance objectives were specified for each program objective [41]. The performance objectives for the first program objective are illustrated in table 2.

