#### Sample size

The sample size was calculated according to the number of cases needed to identify an effect on waist circumference. Waist circumference was chosen over BMI as it is a more sensitive indicator of abdominal fat mass [61]. A previous study indicated that a difference in waist circumference of 1,5 cm between the intervention and control condition may be clinically relevant [43]. In an intention-to-treat analysis, 175 workers per condition are needed to detect a relative difference of 1,5 cm (standard deviation 4,5 cm) in waist circumference with a power of 80% and an alpha of 5%. As workers are clustered within OPs we adjusted for dependence of measurements with an intraclass correlation of 0.20. Taking a loss to follow-up of 20-40% into account among workers and OPs until the final measurement, the initial study population should consist of approximately 300 workers among 10 OPs in each study group (figure 4).

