#### Primary outcome measures

##### Waist circumference

Waist circumference is measured as midway between the lower rib margin and the iliac crest to the nearest 0.1 cm [59,62]. Participants are measured in standing position without heavy outer garments and with emptied pockets, breathing out gently. To standardize waist circumference measurement, OPs or assistants were provided with a Seca 201 waist circumference measure (Seca, Hamburg, Germany). Additionally, waist circumference is measured in a random sample of workers (10-20%) at each measurement by an independent researcher.

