##### Physical activity

Daily physical activity is measured with The Short Questionnaire to Assess Health Enhancing Physical Activity (SQUASH). The SQUASH assesses activities across 4 domains: 1) commuting activities (walking and cycling to/from work), 2) physical activity at work, 3) household activities and 4) leisure time activities (walking, cycling, gardening, chores and sports). Participants are asked to report the number of days per week spent on each activity during an average week in the past month, as well as the number of minutes per day and the intensity of each activity. The SQUASH is a fairly reliable (spearman's correlation coefficient = 0.58) and reasonably valid (spearman's correlation coefficient = 0.45) questionnaire [63]. Total levels of daily physical activity are assessed by two items on the number of days per week moderate intensity activities are performed (such as walking and cycling) for at least 30 minutes (this can be built up by blocks of 10 minutes) and how often per week vigorous intensity leisure time activities ("which make you sweat") are performed during 20 minutes. These items relate to international physical activity guidelines [57] as well as to the Dutch guidelines [64].

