##### Dietary behaviour

Dietary behavior is operationalized as the intake of fruit, vegetables, fruit juice and snacks. These items were selected from the validated Short Fruit and Vegetable questionnaire (validity r = 0.50) [65] and the Fat list (validity r = 0.70) [66]. The number of days per week and the number of daily servings of fruit, vegetables and fruit juice is measured with five items on citrus fruit, other fruits, cooked vegetables, raw vegetables and fruit juice. The consumption of energy dense snacks is assessed by the number of days per week and the number of servings per day in 7 categories (peanuts, chips, cakes, candy bars, biscuits, other cookies and fries). Cut-off points for each behavior are adapted from recommendations of the National Nutrition Centre (The Hague, The Netherlands).

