#### Data analysis

The effectiveness of the weight gain prevention guideline will be analyzed after 6 months (short term) and after 18 months (long term) by means of multilevel analyses. Multilevel analyses accounts for the clustering of observations of workers within the same OP, as well as repeated measurements within one worker. Due to randomization at the OP level, short term data will be analyzed with two levels: 1. worker and 2. OP. Long term data will be analyzed with three levels: 1. time (3 follow-up measurements at 6, 12 and 18 months), 2. worker and 3. OP. Both crude and adjusted analyses will be performed. The multilevel analyses using the follow-up measurement (i.e. 6 months) as dependent variable will be adjusted possible confounders such as, gender, age and education. These variables will also be checked for effect modification. The long-term effect of the intervention will be analyzed using all three follow-up measurements (i.e. 6, 12 and 18 months) adjusted for possible confounders. Effect modification is checked. All statistical analyses will be performed according to an intention-to-treat principle. The investigator analysing the data is blinded to the randomization. A two tailed significance level of p < 0.05 is considered statistically significant. Analyses will be performed with SPSS 15.0 (SPSS Inc. Chicago, Illinois, USA) and MLwiN for multilevel statistical analyses.

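### Three co-equal primary domains at two horizons share one undivided 5% level, although the sample size spends the full 5% on waist circumference alone

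*Protocol article*

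**What the plan says.** - **Primary outcomes.** The Abstract (Methods) says "Primary outcome measures include waist circumference, daily physical activity and dietary behavior". The Phase 2 section on primary outcome measures repeats these three domains and ranks none first.
- **Activity.** The Physical activity section describes two instruments for one construct. It states "The SQUASH assesses activities across 4 domains" and then adds "Total levels of daily physical activity are assessed by two items on the number of days per week moderate intensity activities are performed", with the second item on vigorous activity. No lead summary is named.
- **Diet.** "Dietary behavior is operationalized as the intake of fruit, vegetables, fruit juice and snacks". No composite or lead item is given. Among the programme objectives in Table 1, the dietary ones are fruit and snacks only, and the text of Step 2 agrees: "Regarding nutrition, the consumption of fruit was promoted, and a decrease in consumption of snacks was stimulated".
- **Analysis.** The Data analysis section evaluates effectiveness after 6 months (two-level model) and after 18 months (three-level model using the 6, 12 and 18 month data), each crude and adjusted. It sets one threshold: "A two tailed significance level of p < 0.05 is considered statistically significant".
- **Sample size.** "The sample size was calculated according to the number of cases needed to identify an effect on waist circumference". The inputs are 1.5 cm, SD 4.5 cm, 80% power and 5% alpha, giving 175 workers per condition, with an allowance for losses up to the final measurement.

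**The concern.** A 5% level that applies to each of several co-equal primary outcomes, at each of two horizons, does not hold the overall error at 5%. The sample size section treats waist as if it were the only confirmatory outcome, whereas the outcome and analysis sections do not.

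The consequence is practical. According to Phase 3, adaptation, authorisation and national dissemination of the guideline follow the effectiveness evaluation. If waist is null at both horizons and one self-reported behaviour is significant at one of them, the text gives no basis for saying whether the trial has met its primary aim. The choice would then be open to influence from the results.

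**Working it through.** **Inputs.** Three primary domains (Abstract; Phase 2, primary outcome measures); two horizons and a two-sided 0.05 level (Data analysis); 1.5 cm, SD 4.5 cm, 80% power, 5% alpha, 175 per condition (Sample size). The document gives no correlations between outcomes or between times, so those below are assumptions shown as a range.

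**1. The plan's own figure.** For two means, n per arm = 2 × [(1.960 + 0.842) × 4.5 / 1.5]² = 141.3, so 142 before clustering. The stated 175 lies between 142 × 1.20 = 170.4 and 142 / 0.80 = 177.5. It does not follow from the usual design effect with 17.5 workers per occupational physician: 1 + 16.5 × 0.20 = 4.3, and 142 × 4.3 = 611. That is a separate matter and this point does not depend on it. What matters here is that the 5% is undivided and spent on waist.

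**2. Three domains, one horizon.** If independent, the chance of at least one false positive is 1 − 0.95³ = 0.143. With equally correlated normal test statistics (simulated):

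| Assumed correlation | 0 | 0.2 | 0.3 | 0.5 | 0.7 |
|---|---|---|---|---|---|
| At least one false positive | 14.3% | 14.0% | 13.7% | 12.5% | 10.9% |

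**3. Three domains, two horizons (six tests).** If independent, 1 − 0.95⁶ = 0.265. That is too high, because the long-term model reuses the 6-month data. Assuming a correlation of 0.7 between times:

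| Assumed correlation between domains | 0 | 0.2 | 0.3 | 0.5 |
|---|---|---|---|---|
| At least one false positive | 23.0% | 22.6% | 22.0% | 20.2% |

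**4. Item-by-item testing.** One possible scoring is waist (1), SQUASH total plus two activity items (3) and four dietary items (4), which makes 8 measures. At one horizon this gives 1 − 0.95⁸ = 33.7% if independent, and 31.7% to 19.1% with assumed correlations of 0.2 to 0.7. It is an illustration only, because the article does not say that each item is tested separately.

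**5. What a later repair would do to the stated N.** Splitting alpha over three domains gives 0.05 / 3 = 0.0167. Before clustering, waist then needs 189 per arm instead of 142. Keeping 142 lowers its power from 80% to 66%. Putting waist first at the full 5% leaves the stated calculation untouched.

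**The case against.** The strongest case against is that this is a condensed article. Hierarchy, scoring and alpha allocation commonly sit in the full protocol or analysis plan, which are not shown, and sizing a trial on one of several outcomes is not in itself an error. That stands as far as missing scoring detail goes. It does not dispose of the point, because the article states both the set of co-equal primaries and the undivided threshold, and it states a sample size that leaves no room for a later alpha split.

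Several stronger readings are tempting, and the document does not support them:

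- **Eight measures, sixteen tests, 56%.** A reader might multiply 8 measures by 2 horizons and compute 1 − 0.95¹⁶ = 56%. The count of eight depends on scoring: the fruit, vegetable and juice items could be combined, and the two activity items could form one guideline-adherence outcome. The 56% also assumes independence, although the two horizons share data.
- **Success on any one outcome counts.** This is inference. The text gives neither an any-outcome nor an all-outcomes rule.
- **Vegetables and juice are outside the trial.** They have no programme objective, but vegetable intake is part of the eligibility definition. The Dietary behaviour section also refers to recommended cut-offs for each behaviour, so it cannot be said that juice lacks a reference standard.
- **False positives are likelier on self-report because of reporting bias.** This is a separate issue that no multiplicity rule cures. Waist is itself measured by the occupational physicians or their assistants, with an independent check in only 10-20% of workers.

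Behavioural primaries do match the programme objective of stimulating activity and healthy diet. That argues for keeping them in the confirmatory sequence; it does not argue for testing each at an unshared 5%.

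**Conclusion.** The point holds at the level of the three stated domains. The chance of at least one false-positive primary result is 14% if the three tests are independent, and about 11-14% under assumed correlations of 0.2-0.7. Over both horizons it is about 20-23%, assuming 0.7 between times and 0-0.5 between domains. Each of these is at least twice the nominal 5%. Testing activity and diet item by item, or choosing between crude and adjusted results, could only raise the figure, by an amount the document does not allow one to fix.

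The calculation takes the 5% threshold to apply separately to each primary domain at each horizon, as the Data analysis section reads. If the full protocol or analysis plan already sets a hierarchy, the article should be brought into line with it.

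**What to change.** In the Data analysis section:

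1. Name waist circumference at one stated horizon, in one stated model (crude or adjusted, with the covariates listed), as the first, confirmatory test at two-sided 5%. The final measurement fits the loss allowance in the Sample size section. If it is chosen, say whether the test is the 18-month difference or an average over the three follow-ups.
2. If waist is significant, test one named activity summary and the two dietary behaviours targeted in Table 1 (fruit and snacks). Use a fixed order at 5% each, or Holm across the three, with a first step of 0.05 / 3 = 0.0167.
3. Report the remaining items, the other horizon and the other models as supportive.

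**Cost.** No extra participants are needed, and the stated alpha and N for waist are unchanged. Activity and diet can be claimed only after waist succeeds and under a stricter rule. The trial is registered and the occupational physicians are already randomised, so this is a substantive change to the primary outcomes. It should be documented as an amendment, with the registration aligned, before the analysis is unblinded.

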**Discussion:**

Improving workers' daily physical activity and dietary behavior may prevent weight gain and subsequently improve workers' health, increase productivity, and reduce absenteeism. After an effect- and process evaluation the guideline will be adjusted and, after authorisation, published. Together with several implementation aids, the published guideline will be disseminated broadly by the Netherlands Society of Occupational Medicine.

**Trial Registration:**

ISRCTN73545254/NTR1190

## Background

Overweight is one of the world's most challenging public health problems [1]. The prevalence of overweight has reached epidemic proportions in most Western countries, including the Netherlands. Currently, over 30% of the Dutch working population is overweight and around 6% is obese [2]. The prevalence of overweight is expected to increase substantially over the next years [3]. The average gain in weight is calculated to vary between 0.4-0.9 kg per year [4,5]. This trend is a cause for concern as overweight has been associated with an increased risk for type 2 diabetes, cardiovascular diseases, and some cancers, as well as with higher absenteeism rates and lower productivity levels [6-9]. Consequently, the overweight-related mortality, direct costs (health care costs) and indirect costs (costs of sick leave, loss of production) may increase [10,11].

Despite worldwide awareness of the obesity epidemic, tackling this public health problem remains difficult [12]. Individual treatment of overweight subjects has proven difficult because the large behavioral changes necessary for weight loss are difficult to achieve. Moreover, body weight is often regained on the long term [13,14]. Population-based prevention of weight gain, aimed at personal and environmental factors, may prove to be more efficient.

Overweight is the result of a gradual gain in weight over time as energy intake (i.e. dietary behavior) exceeds energy expenditure (i.e. physical activity). In order to prevent weight gain, a small change of 100 kcal/day is assumed necessary, which may be walking 2000 steps more per day or replacing an energy dense snack by a healthier snack [15]. This may best be achieved by inducing small behavior changes because these are more feasible to achieve and maintain [16].

The workplace is considered an appropriate setting for lifestyle promotion, as a major part of the adult population can be reached [2]. In the Netherlands, employees can be reached through health risk appraisals conducted by occupational physicians (OP). This voluntary health risk appraisal, which may consist of anthropometric measurements (such as body composition, aerobic fitness and blood values) and a subsequent advice by the OP, makes both research and intervention feasible among Dutch employees. An extensive literature study concluded that primary prevention lifestyle interventions are effective and feasible within the Dutch occupational health setting [17]. Nevertheless, OPs hardly implement weight gain prevention interventions due to a lack of knowledge and evidence-based methods and strategies. To date, activities of OPs are predominantly aimed at reducing absenteeism. Moreover, of the few OPs who do implement preventive interventions, the strategies vary and are not based on the current evidence. Based on the literature study and additional interviews, it was concluded that a need exists among OPs how to promote physical activity and dietary behavior in an effective way.

The Netherlands Society of Occupational Medicine recognises the need for improvement of the professional quality of the OPs and thus emphasises the need for a clinical practice guideline. Practice guidelines are systematically developed statements, designed to assist physicians with decisions about appropriate health care for specific clinical circumstances [18]. Practice guidelines consist of 1) a guideline text, which is formulated as a structured stepwise sequence of recommendations for practice, 2) a one page summary leaflet and 3) a background document, in which the levels of evidence for the recommendations are indicated and reference to the most important literature is given. The systematic development, evaluation and implementation of a weight gain prevention practice guideline in a careful and well-designed process is thus innovative and of major relevance. In order to perform a proper cost-, effect- and process evaluation of the guideline, the evaluation of the guideline is conducted in a randomised controlled trial. The Balance@Work project consists of three phases: phase 1. development, phase 2. evaluation, and phase 3. implementation of an occupational health guideline aimed at the prevention of weight gain among employees. This paper describes the development of an occupational health guideline, the design of the evaluation and the design of the implementation.

## Methods

### Phase 1. Development of the weight gain prevention guideline

For the systematic development of the weight gain prevention guideline and associated intervention, the practice guideline development protocol of the Netherlands Society of Occupational Medicine was applied in combination with the Intervention Mapping (IM) protocol [19,20] (Figure 1a and 1b). Both protocols facilitate a stepwise process for theory- and evidence based development of guidelines and health promotion interventions respectively. In phase 1 we describe our approach to each step applied to the prevention of weight gain among employees, focusing particularly on steps 1-4 of the IM protocol. As all steps of the Netherlands Society of Occupational Medicine protocol complement those of the IM protocol, these steps were incorporated in phase 1.

**Figure 1 F1:**
[figure not shown]
**1a Guideline development protocol of the Netherlands Society of Occupational Medicine **[19]. 1b - Intervention mapping protocol [20].

